## Abstract

**Background:**

Professionals need adequate tools to help patients with diabetes and depression. Although web programs integrating cognitive-behavioral therapy with diabetes education have shown good results, no similar approach has been performed as yet in Spain. The objective is to develop an Internet-based program for the treatment of mild-moderate depressive symptomatology in individuals with type 1 diabetes (WEB_TDDI1 study) based on Cognitive-behavioral therapy (CBT) and assess its results.

**Methods:**

A 2-arm randomized controlled trial will be conducted. Adults with type 1 diabetes and mild-moderate depressive symptoms will be screened to participate in the study and randomly assigned to either the treatment group (TG) that will use a Web-based application for a specific 9-week intervention in depression and type 1 diabetes or the control group (CG) that will be on the waiting list during that time.

**Results:**

Data on the primary variable (depressive symptoms) and secondary variables (treatment-related distress, anxiety, fear of hypoglycemia, quality of life, treatment adherence, coping strategies and glycemic control) will be collected from the TG at the beginning/baseline, at the end of treatment and at 3, 6 and 12 months after treatment. The CG will be assessed at the beginning and at the end of the TG intervention. On completion of the program by the TG, the treatment will then be carried out in the CG.

**Conclusions:**

The new web application developed is expected to be effective for the treatment of mild-moderate depressive symptoms in adults with type 1 diabetes, reducing depressive symptoms and improving the rest of the analyzed variables.

**Trial registration:**

Registry: NCT03473704 (March 21, 2018); ClinicalTrials.gov.

## Introduction

The risk of depression is 3 times higher in individuals with type 1 diabetes than in the general population [1]. The presence of both diseases increases the number of complications resulting from diabetes [2, 3], decreases adherence to diabetes treatment [4, 5] and increases healthcare costs compared to individuals with diabetes who do not have depression [6, 7]. Consequently, early detection and proper treatment is especially important. However, only 25% of people with diabetes and depression are identified during their visit to the doctor [8] and, therefore, 75% may not have access to correct treatment.

According to a study conducted by Anarte et al., [9] which examined the accuracy of the physician in detecting depression in patients with type 1 diabetes, 25% of patients with depression were not identified. The difficulty of identifying this disorder in the population with diabetes results in treatment being delayed or possibly not even provided. Petrak et al. [10] stress the importance of the correct treatment of depression for good diabetes self-care, as individuals with diabetes may adhere to their treatment more easily if they are in a good mood.

Research confirms that treatment of depression in people with diabetes is effective [11, 12]. The interventions that have been carried out for the treatment of depression in diabetes consist of psychological interventions, psychopharmacological treatments, dietary treatments and physical activity. Psychological intervention has shown better results than usual care and waiting list in reducing positive symptoms [10] Cognitive-behavioral therapy (CBT) is one of the psychological interventions used. This therapy is an effective treatment for adults with depression [13].

The evidence available through 4 meta-analyses of the main randomized controlled trials [14–17] and one systematic review [18] indicates that CBT is effective in treating depression in individuals with diabetes.

With the rise of new technologies among the population, new forms of treatment through the Internet are now possible, offering great advantages over traditional treatments, such as accessibility, reducing the stigma of diabetes and therapist interaction time while still maintaining effectiveness [19]. Internet-based treatment has been shown to be effective for depression [20], as it has been for other chronic diseases [21], although additional research on its long-term effect is needed [22]. Two pioneering platforms for the general population that have obtained positive results are MoodGYM and Beating the Blues [23, 24]. In Spain, an Internet platform based on CBT called Smiling is Fun has been created for primary care, demonstrating a benefit when implemented together with usual care [25]. The use of Internet-based CBT has also been shown to be effective in the treatment of depressive symptoms [26].

In diabetes, the use of new technologies allows easy access to a greater number of users [27]. Application of these technologies has been shown to be a good tool in the treatment of depression yielding positive results [28]. For the treatment of depression in people with diabetes, several authors have designed web programs incorporating CBT. In the first study carried out for this purpose, van Bastelaar et al. [29–31] designed and administered a specific treatment program for people with diabetes that comprised 8 sessions comparing the results with those of a control group that received no treatment. They obtained positive results in depression and specific distress but not in glycemic control. Based on the work of van Bastelaar et al., [29–31] Nobis et al. [32–34] developed a web-based intervention with telephone support for adults with diabetes. In this case, the results of the 6-session web treatment (plus 2 optional sessions) were compared with a psychoeducation program. Again, there was an improvement in depression and diabetes-specific distress in the intervention group, although there were no changes in glycemic control. The benefits found were maintained at the 6-month follow-up.

Other authors have assessed the effectiveness of Web-based CBT treatment programs for the general population in individuals with diabetes. Robins et al. [35] designed a study in which they compared a 6-session Web-based treatment for the general population with a control group treated with usual treatment, obtaining positive results in mood and diabetes-specific distress, among others, but not in glycemic control. These results were maintained after 3 months of follow-up [36]. Clarke et al. [37] designed a study to evaluate the effect of a general population CBT program (myCompass) on the well-being of young people with type 1 diabetes. The results of this study have not yet been published. Nevertheless, they analyzed the results of this 7-session program in a pre-post study without a control group in a population with type 1 and type 2 diabetes and found significant improvement in depressive symptoms and specific distress, among other variables, although data on glycemic control were not collected [38] Thus, these treatment programs could also be offered as a possible avenue of intervention in people with diabetes.

According to previous studies, 21.7% of people with type 1 diabetes in our population have depressive symptoms [39]. There is a clear need to provide professionals with adequate tools to help people with this problem.

Based on the results obtained in previous studies, we have developed an Internet-based program for the treatment of mild-moderate depressive symptomatology for individuals with type 1 diabetes (WEB_TDDI1 study). In this study, we have created a specific program for people with type 1 diabetes including specific modules aimed at improving depressive symptomatology in this population and, indirectly, other variables related to depression in diabetes such as coping, anxiety, distress, and fear of hypoglycemia, which affect glycemic control, adherence to diabetic treatment and quality of life. This program has been designed specifically for individuals with type 1 diabetes because there are differential characteristics between type 1 and type 2 diabetes that should be considered separately [40] There are also important differences in their association with depression, suggesting that the associations are mediated by different underlying mechanisms [41] This article presents the design of this program and the methodology for its development and assessment.

The main objective of this project is to apply an internet-based program for the treatment of depression specific to individuals with type 1 diabetes. The program, designed by our research team (WEB_TDDI1 study), will be implemented in a sample of patients with type 1 diabetes and mild-moderate depressive symptoms in the province of Malaga (Spain).

## Material and methods

### Study design and participants

This study is a longitudinal randomized control-group pretest-posttest clinical trial (S1 Table). Patients with type 1 diabetes who present depression (mild to moderate) and meet the inclusion criteria will be randomized through a computer program to 2 groups. The treatment group (TG) will receive the 9-week Web-based treatment, while the control group (CG) will comprise patients on the waiting list. Evaluations in the TG will be conducted at the beginning of the program (baseline), at completion and during follow-up (3, 6, and 12 months) after treatment. For ethical reasons, the CG will receive the Web-based treatment once the TG intervention has been completed. The CG will thus be assessed at the beginning and at the end of the TG treatment. At this point, the CG will begin treatment, provided the participants still meet the eligibility criteria, and will have their corresponding evaluations. The assessments will be conducted in person.

The participants will be individuals with type 1 diabetes from the province of Malaga (Spain) who meet the following criteria:

○ Inclusion criteria: medical diagnosis of type 1 diabetes ≥ 1 year; over 18 years of age; psychological diagnosis of mild/moderate major depressive disorder, dysthymia or depressive symptomatology; no concomitant pharmacological treatment that could modify blood glucose values or depressive symptomatology; no psychological treatment at the present time; absence of the following: chronic renal failure, impaired liver function tests, active thyroid disease (except correctly substituted hypothyroidism), current pregnancy or acute ketosis decompensation at the beginning of the study; Internet access.○ Exclusion criteria: type 2 diabetes; women who are pregnant or planning to become pregnant; severe macrovascular or microvascular complications; diagnosis of major depressive disorder with risk of suicide; non-collaboration (no signed informed consent); presenting a disabling psychiatric disorder; psychosis; no Internet access.

All participants in this study must give their informed consent. The ethical standards of care in the provision of telepsychology services of the General Council of Psychology of Spain [42] will be followed. The project will be carried out following the guidelines of the Declaration of Helsinki and the Standards of Good Clinical Practice. Personal data will be processed according to the LOPD. This study has been approved by the Ethics Research Committee Provincial de Malaga (Approval number: 1216/PIA14), Spain (December 20, 2016) and has been registered in ClinicalTrials.gov with ID NCT03473704 (March 21, 2018).

All the data collected in this study will be recorded anonymously, strictly following the laws and data protection regulations in force (Law 41/2002 of November 14; Law 15/1999 of December 15).

In order to protect the confidentiality of the personal information of the participants, the following measures have been taken: all the data that can identify the participant will be kept separate from the rest of the information collected in the different questionnaires of the study; each case of the study will have an identification number that will be the one that appears in the databases; the information analysis will always be done in an aggregate way and never individually; all researchers involved in the project undertake to comply with the necessary standards to preserve the confidentiality of the information provided by the participants; personal data will be permanently unlinked from study data in order to protect the identity of the participants (data anonymization method); all study databases will be electronically protected with codes that limit access only to project researchers.

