#### Procedure

The participants will be individuals with type 1 diabetes who regularly attend consultations in the Clinical Management Unit of Endocrinology and Nutrition of 2 hospitals (tertiary care) and a specialty center (secondary care) of the Andalusian Health Service of the province of Malaga (Spain) who voluntarily choose to participate in the study. The participants will not receive any type of economic or material remuneration.

Patients will be recruited through information posters placed in the visible areas of the Units, inviting them to participate in the study, either directly by sending an e-mail or through their physician. Those interested in participating will be evaluated by a psychologist from the research group who will assess the inclusion and exclusion criteria. Depressive symptoms will be evaluated with the Beck Depression Inventory-FastScreen (BDI-FS) [43] Patients with a BDI-FS score greater than or equal to 4 and less than 13 who meet the rest of the inclusion criteria and none of the exclusion criteria will sign the informed consent. All questions about the study will be answered, and the necessary aspects clarified, ensuring that the participant has understood everything he or she has read. The participants will then be prepared to begin the study and the initial assessment will be conducted.

Once the sample has been randomized, the participants will be notified of the group to which they have been assigned by e-mail. Those assigned to the CG will be given encouragement while they wait to begin treatment after the TG has completed the treatment (Fig 1).

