Clinical data and glycemic control will be collected through the medical record form of the visit to the physician and the data provided by the participant.

The primary variable is depression. Depressive symptoms during the previous 2 weeks will be assessed through a self-administered 7-item questionnaire (0–3), the BDI-FS [43]. For the diagnosis of depression, the Structured Clinical Interview for Major Depression Episode of the DSM-V will be used [44].

Among the secondary variables, fear of hypoglycemia will be evaluated with the Fear of Hypoglycemia questionnaire (FH-15) [45], which consists of 15 negative items on a Likert-type scale (1–5), and diabetes-related distress using the Spanish version [46] of the Diabetes Distress Questionnaire (DDS) by Polonsky et al., [47] which has 16 Likert-type items (1–5). The DDS provides a total distress score and 4 specific scores: affective distress; distress associated with the doctor-patient relationship; regimen-related distress and interpersonal distress. Quality of life will be assessed with the Diabetes Quality of Life Questionnaire [48], which evaluates quality of life specifically in individuals with diabetes mellitus. The Spanish version [49] has 43 questions (1–5) and 4 subscales: Dissatisfaction, Impact, Social/vocational concern and Concern for future aspects. Anxiety will be addressed using the Spanish version [50] of the State-Trait Anxiety Inventory (STAI) [51]. The STAI consists of 2 scales: State Anxiety (STAI-S) and Trait Anxiety (STAI-T). Each scale includes 20 self-administered items (0–3). Coping will be evaluated with the Spanish version [52] of the COPE inventory [53], composed of 5 scales assessing problem-centered coping, another 5 scales measuring emotion-centered coping, and 3 scales measuring less useful coping responses. Adherence to treatment will be evaluated with the 15-item (1–5) Spanish version of the Diabetes Self-Care Inventory-Revised questionnaire [54]. Personality will be evaluated using the Millon Clinical Multiaxial Inventory-III Spanish version [55]. This questionnaire contains 175 items with true or false answers. It consists of 11 basic personality scales, 3 pathological characteristics scales, 7 moderate syndrome scales and 3 severe syndrome scales.

The results of the trial will be published in peer-reviewed journals and presented in conferences.

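### Control participants' access to the programme appears to depend on the same self-reported score that serves as their primary outcome, which may bias the only randomised comparison

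*Protocol article*

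**What the plan says.** All references are to the protocol article.

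- **Timing of the control assessment** (Study design and participants): "The CG will thus be assessed at the beginning and at the end of the TG treatment".
- **Access rule** (next sentence of the same section): "At this point, the CG will begin treatment, provided the participants still meet the eligibility criteria, and will have their corresponding evaluations".
- **Entry window** (Procedure): "Patients with a BDI-FS score greater than or equal to 4 and less than 13 who meet the rest of the inclusion criteria" go on to consent, provided no exclusion criterion applies. In whole scores the window is 4 to 12.
- **Primary measure** (Results assessed): "The primary variable is depression", and depressive symptoms "will be assessed through a self-administered 7-item questionnaire (0–3), the BDI-FS". The possible total is 0 to 21 (7 × 3).
- **Knowledge of allocation** (Procedure): after randomisation "the participants will be notified of the group to which they have been assigned by e-mail".
- **Statements without the condition**: the abstract's Results paragraph says "On completion of the program by the TG, the treatment will then be carried out in the CG". Earlier in the Study design paragraph, the control group is likewise given the programme, on ethical grounds, with no condition attached.

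**The concern.** The control group's post-treatment visit does two jobs. It supplies the outcome for the between-group comparison, and it is the point at which access to the programme is decided. If the entry criteria are re-applied in full, a control who has improved to a score of 0 to 3 no longer qualifies. Someone who volunteered for treatment, has waited through the nine-week programme and knows the rule has a reason to score at least 4. A TG participant has already had the programme, so nothing comparable hangs on the answer.

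The measure is self-reported and allocation is known, so nothing in the measurement itself guards against this. Nor can a later visit correct it: the controls start treatment after this assessment, and the 3-, 6- and 12-month visits have no untreated comparator. At stake is the credibility of the trial's one randomised contrast on its primary variable.

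**Working it through.** **Is the link in the text?**

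1. The control assessment and the access decision fall at the same point (consecutive sentences in Study design and participants).
2. Eligibility requires a depressive disorder or depressive symptomatology (same section), made operational as BDI-FS 4 to 12 (Procedure).
3. The BDI-FS measures the primary variable and is self-administered (Results assessed).
4. Participants know their group (Procedure).
5. The article does not separate the access decision from the outcome score.

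Step 2 involves one inference: the article does not say outright that the BDI-FS window is re-applied. It is the natural reading of a requirement to go on meeting the criteria.

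**Which way does the incentive point?**

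| Control's true score at the visit | Position under the rule | Incentive if the rule is known |
|---|---|---|
| 0 to 3 | below the window | report more |
| 4 to 12 | inside the window | none |
| 13 or more | above the window | report less |

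The worsening rule in the Intervention section (severe depression or suicidal ideation leads to discontinuation) adds to the pressure in the last row. Everyone enters with mild to moderate symptoms, so I judge the first row likely to outweigh the third, but the article gives no expected distribution to confirm this.

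**How large could it be? (illustration)**

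The plan gives no figure on this point to reproduce. From the plan I take 28 per group (Sample size calculation) and Student's t-test (Statistical analysis). That 28 is not reproduced for a two-group comparison at d = 0.50 and 80% power, which needs 64 per group two-sided. This is a separate matter; 28 is simply the planned number here. The plan states no sidedness, so a two-sided 5% test is assumed, with 2.5% in each direction.

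If the programme has no effect and the control mean is shifted up by b SD:

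- degrees of freedom = 28 + 28 − 2 = 54; critical t = 2.005
- noncentrality = b × √(28/2) = b × 3.742
- false positives in favour of TG = P(T > 2.005), T noncentral t

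| b (SD) | Noncentrality | False positives favouring TG |
|---|---|---|
| 0 | 0 | 2.5% |
| 0.1 | 0.374 | 5.6% |
| 0.2 | 0.748 | 11.0% |
| 0.3 | 1.122 | 19.6% |

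**What would a shift of that size require?** The shift is (net share of controls inflating × points added) / SD. The document gives no BDI-FS SD and no such share. Assume 2 points added per person and an SD of 2 to 4:

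| Net share inflating | Mean shift (points) | SD = 2 | SD = 3 | SD = 4 |
|---|---|---|---|---|
| 10% | 0.2 | 0.10 | 0.07 | 0.05 |
| 20% | 0.4 | 0.20 | 0.13 | 0.10 |
| 30% | 0.6 | 0.30 | 0.20 | 0.15 |

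A shift of 0.05 SD gives 3.8%, so the low corner of this table is nearly harmless. Reaching 0.3 SD with an SD of 4 would take 0.3 × 4 / 2 = 60% of controls, which is hard to credit. The share is net: each control at the top of the window who under-reports by 2 points cancels one who over-reports by 2.

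**The case against.** The strongest reply is that the mechanism needs knowledge that the article does not show controls to have: that access is conditional, that the BDI-FS counts, and roughly where the cut-off lies. What it says they hear points the other way. They are encouraged while they wait, and are told the next start date by telephone or e-mail. If they believe access is assured, the incentive disappears. This stands, and it limits the point to a risk.

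Second, the window has an upper limit and there is a worsening rule, so the pressure is to stay within 4 to 12, not to score as high as possible. This also stands. It weakens the claim of direction without removing it.

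Third, the BDI-FS is not shown to be the sole test. A psychologist assesses the criteria at entry, assessments are in person, and the structured clinical interview is scheduled at every time point. True, but a score below 4 would still fail one necessary criterion.

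Fourth, a reader might infer that the article flatly contradicts itself on whether controls are treated. It does not go that far. The condition follows shortly after the general statement in the same paragraph and can be read as qualifying it, and an abstract condenses. The wording is unclear and needs reconciling, but this is not a hard contradiction.

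**Conclusion.** The concern holds as a design risk. The rule, read naturally, lets the post-treatment BDI-FS decide a control's access to the programme as well as measure the primary outcome, and only controls face that consequence. This may bias the comparison, and the net direction is probably in favour of TG.

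A reader might infer more: that the rule does bias control scores, only upward, and by a known amount. The documents do not support that. Whether participants know the condition is not stated, the upper limit pulls some scores the other way, and the figures of about 6% to 20% follow from assumed shifts of 0.1 to 0.3 SD, not from trial data. They show that a modest shift would matter with 28 per group; they do not show that one will occur.

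This is a cheap improvement to the only randomised contrast.

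**What to change.** 1. Reconcile the conditional sentence in Study design and participants with the unconditional statements in that paragraph and in the abstract, so that the terms of control access are stated once and consistently.
2. State that the post-treatment BDI-FS outcome score does not decide access.
3. Make any access check separately, after the outcome has been recorded, using information already collected at the visit other than that score.
4. Tell participants before the visit that their questionnaire answers do not affect whether they get the programme.

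Which clinical conditions govern access, including treatment started while waiting and the handling of worsening mood described under Intervention, is for the investigators to settle.

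The cost is a wording change in the protocol and participant information. The downside is that a few of the 28 controls, now below the cut-off, may use therapist time and add near-floor scores to the control group's own later pre-post evaluations. The randomised comparison is not affected by that, because its outcome is recorded first.

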Therapists will send e-mails to the TG participants to encourage them to continue their efforts and they will be called if there is no response to these e-mails. Halfway through the program, their opinions about it will be sought (doubts, suggestions for improvement). This is intended to motivate the participants in order to improve adherence and minimize the risk of drop out.

The CG (waiting list) participants will receive a telephone call or e-mail informing them of the next program start date. In the event that during the study an individual (CG or TG) is found to have a worsening depressive mood (severe depression or suicidal ideation), the participant would discontinue the study and his or her physician would be notified in order to refer the individual to the Clinical Management Unit of Mental Health of the Andalusian Health Service.

Protocol amendments: Important protocol modifications will be reported to the researchers, the University of Malaga and the protocol registry.

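### The entry exclusion for suicide risk covers only major depressive disorder, although dysthymia and depressive symptomatology also qualify for randomisation, including to the 9-week waiting list

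*Protocol article*

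**What the plan says.** All references are to the Protocol article.

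- **Who qualifies** (Study design and participants, inclusion criteria): "psychological diagnosis of mild/moderate major depressive disorder, dysthymia or depressive symptomatology".
- **Treatment status at entry** (same list): "no concomitant pharmacological treatment that could modify blood glucose values or depressive symptomatology; no psychological treatment at the present time".
- **Suicide risk at entry** (same section, exclusion criteria): "diagnosis of major depressive disorder with risk of suicide". The other psychiatric exclusions are a disabling psychiatric disorder and psychosis; neither names suicide risk.
- **Screening** (Procedure): "Those interested in participating will be evaluated by a psychologist from the research group who will assess the inclusion and exclusion criteria". A BDI-FS total of at least 4 and below 13 is also required.
- **After consent** (Procedure): "The participants will then be prepared to begin the study and the initial assessment will be conducted". Randomisation follows.
- **Control condition** (Abstract, Methods): "the control group (CG) that will be on the waiting list during that time". The Procedure section adds: "Those assigned to the CG will be given encouragement while they wait to begin treatment after the TG has completed the treatment".
- **In-study rule** (Intervention): if "during the study an individual (CG or TG) is found to have a worsening depressive mood (severe depression or suicidal ideation"), that person leaves the study and the physician is notified so that a mental health referral can be made.

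**The concern.** The inclusion list treats major depressive disorder, dysthymia and depressive symptomatology as three separate ways in. The suicide-risk exclusion is attached to the first only. Because the same criteria list draws the distinction, the exclusion cannot simply be taken as shorthand for any depression.

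What is at stake is patient safety; no estimate or analysis is affected. A person at risk without major depressive disorder could be admitted on the written criteria. If assigned to the control group, that person starts the wait with no psychological treatment and no drug that could change depressive symptoms, since both are conditions of entry. During the wait the article describes encouragement and contact about the start date. The in-study withdrawal and referral rule does cover the control group, but control assessments are scheduled only at the beginning and end of the treatment group's programme, so no scheduled assessment in between would detect a problem.

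**Working it through.** The article gives no figure for suicide risk to reproduce, so the check is a comparison of its rules.

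**Step 1. Scope of entry against scope of exclusion.**

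| Qualifying state | Admitted | Exclusion naming suicide risk applies |
|---|---|---|
| Major depressive disorder, mild or moderate | yes | yes |
| Dysthymia | yes | no |
| Depressive symptomatology | yes | no |

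**Step 2. Whether another entry rule fills the two empty cells.** The disabling-disorder and psychosis exclusions may catch some people but do not name suicide risk. The psychologist is asked to assess the listed criteria, which are these same criteria. The BDI-FS rule works on the total. The questionnaire has 7 items scored 0 to 3 (Results assessed), so the maximum is 7 × 3 = 21 and the admitted range is 4 to 12. One item at its maximum of 3 needs between 4 − 3 = 1 and 12 − 3 = 9 points from the other six, which can supply up to 6 × 3 = 18. Any single item can therefore be at its maximum inside the window. The article does not say what the items ask, so this shows only that a total-score rule cannot replace a suicide-risk rule.

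**Step 3. Whether the in-study rule acts before allocation.** The Procedure section gives this order:

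1. Psychologist's evaluation: no consent yet, so only the eligibility criteria act.
2. Informed consent.
3. Initial assessment: the in-study rule could be read to apply here.
4. Randomisation.

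The in-study rule speaks of mood that has worsened, during the study, in a member of one of the two groups. At step 1 it does not operate. At step 3 its wording does not clearly reach ideation that was already present before a group was assigned.

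**Step 4. Consistency.** Once a person is in the study, suicidal ideation leads to withdrawal and referral whatever the diagnosis. At entry, suicide risk excludes only with one diagnosis. The entry rule is the narrower of the two.

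**Step 5. Exposure to the waiting list.** Sample size calculation plans 28 per group and 56 in total. Share assigned to the waiting list = 28/56 = 0.50, assuming equal allocation as the equal group sizes imply. This share holds for every participant and says nothing about how many are at risk. The article gives neither the mix of diagnoses nor the frequency of suicide risk, so that number cannot be calculated.

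**The case against.** The strongest reply is that the gap is narrow in practice and that the in-study rule may already close it. A person who has consented and is at the initial assessment is arguably in the study; the parenthesis in that rule can be read as making suicidal ideation itself the trigger; and the mention of both groups may mean only that neither is exempt. On that reading it would be odd for staff to find ideation at baseline, randomise anyway, and then withdraw the person. Several safeguards also precede randomisation: a psychologist sees every candidate, the BDI-FS total is capped, baseline includes a structured clinical interview for a major depressive episode, assessments are in person, and the project has ethics approval. Participants also attend endocrinology consultations regularly, and nothing says that care would be refused if a need arose. Finally, this is a condensed article, and details of risk assessment may sit in the full protocol.

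Much of this stands as mitigation. It supports the view that few people would be affected, and the 50% should not be read as a measure of harm. It does not remove the point. The reading of the in-study rule at baseline is possible but not clear, and it does not reach the evaluation before consent. The safeguards depend on clinical judgement going beyond the written list. Nor is this a complaint about omitted detail: the criterion is printed, and its scope is too narrow.

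**Conclusion.** The concern holds as a point about the written criteria. A person with dysthymia or depressive symptomatology who is at risk of suicide meets no stated exclusion on that ground and can be randomised. With equal allocation, such a person has a 28/56 = 50% chance of the 9-week waiting list. The number affected is unknown and probably small.

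The conclusion rests on reading the exclusion literally and on the in-study rule not clearly covering ideation present before allocation. The change should be made, because it concerns safety and brings entry into line with the trial's own in-study rule. Confidence is medium, given the screening by a psychologist and the possible wider reading of the in-study rule.

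**What to change.** Replace the exclusion with: *risk of suicide or current suicidal ideation, whatever the depressive diagnosis*. Apply it at the psychologist's evaluation and again at the initial assessment, both before randomisation. Refer anyone excluded by the route already set out under Intervention: physician notified, referral to the mental health unit. The method of assessing risk can stay in the full protocol.

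The cost is one line in the eligibility criteria. Both assessments and the referral route are already planned, so no new procedure is needed. The downside is possibly a few more screen failures.
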